## Statistical analysis plan

The Leicester Clinical Trials Unit (LCTU) statistician will be responsible for planning, monitoring and carrying out data analyses throughout the study, supervised by the senior LCTU statistician ([name]). Statistical analysis will be undertaken according to a pre-specified statistical analysis plan written prior to database lock and reported following CONSORT statements (20).

## Summary of baseline data

Data collected at baseline will be presented as means and standard deviations or medians and ranges if not normally distributed for all continuous variables and/or number and percentage for categorical variables, overall and by randomised group. No formal statistical hypothesis tests will be used to assess normality assumptions or make comparisons of differences between groups.

## Primary outcome analysis

The primary analysis of the primary outcome (amputation free survival) will compare the time to first event between randomised groups. The primary outcome will be defined as time to first event calculated by measuring in days the time from randomisation until first event or last known event-free observation during the follow-up period. Participants not experiencing a primary outcome event will have their time to event censored at last follow-up date. Participants withdrawing consent or that are lost to follow-up prior to reaching primary outcome will have their time to event at last contact date. The primary analysis will be undertaken on an intention-to-treat basis with all participants included post randomisation analysed in the group to which they were allocated. The primary outcome will be compared between randomised arms using restricted mean survival time carried out using a validated programme such as the Stata module ‘STRMST2’ or equivalent. A point estimate, 95% confidence interval and 2 sided p-value will be presented. Statistical significance will occur if the p-value is <0.05. The primary analysis will be adjusted for the minimisation factors used at randomisation. The individual components of the primary outcome will be reported separately as secondary outcomes

Secondary analyses of the primary outcome will explore a per-protocol population excluding major protocol deviators.

## Secondary outcome analysis

Secondary outcomes will be analysed on a complete case population using appropriate methods: restricted mean survival time or cox proportional hazards regression (as appropriate) for time-to-event outcomes, logistic regression for binary outcomes, linear regression for normally distributed continuous outcomes or where not normally distributed using appropriate non-parametric methods and mixed effects models with participant as random effect where outcomes are repeated measures over time, all adjusted as described and presented as point estimates with 95% confidence intervals in the intention to treat population.

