## Economic impact and cost effectiveness

We obtained information from our published meta-analysis (1) and HES to identify patients with CLTI/claudication and TASC C/D aorto-iliac disease who had revascularisation between 2014-2019. We then constructed an early decision model to calculate 3 year death, amputation, and re-intervention rates, NHS resource use, and quality-adjusted life years (QALYs). Open surgery is associated with a peri-operative mortality of 3% vs. 1% for endovascular treatment. The latter is associated with more re-interventions and late amputations/deaths. Three year survival is 70% for open surgery vs. 65% for endovascular treatment (HES data). Open surgery costs arise from intensive care stay and early complications. Endovascular treatment costs arise from devices, re-interventions, and late amputations. Average peri-operative and device costs are £13,765 for endovascular treatment. Late re-interventions and amputations cost £6,811, totalling £20,576 for endovascular treatment over 3 years. Open surgery costs £10,675 over 3 years (£9,901 less per patient). The 3 year QALY difference is 0.153, favouring open surgery, despite the higher immediate mortality/morbidity. All of these estimates, however, are based on unadjusted observational data. Overall, it is very uncertain whether endovascular treatment, despite being minimally invasive, is cost-effective in the NHS.

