## Secondary outcomes

Secondary outcome measures are:

1. Mortality (all cause), measured in days from randomisation until first event or until the end of the trial (minimum 2 years) where no event occurs
2. Cardiovascular events (myocardial infarction, stroke, admission for heart failure), measured in days from randomisation until first event or until the end of the trial (minimum 2 years) where no event occurs
3. Number of hospital admissions (including reasons for readmissions), following discharge from index surgical admission for up to 4.5 years
4. Number of re-interventions (including nature of re-intervention), following index surgical procedure for up to 4.5 years
5. All lower limb amputations (minor and major i.e. below and above ankle joint) measured in days from randomisation until first event or until the end of the trial (minimum 2 years) where no event occurs
6. Concomitant medications (specifically: use of statin, use of antithrombotic medication)
7. Estimated glomerular filtration rate (renal function) based on serum creatinine levels using the Chronic Kidney Disease Epidemiology (CKD-EPI) formula measured at 6 and 12 months and annually thereafter
8. Low Density Lipoprotein measured at 6 months
9. HbA1C measured at 6 months
10. Cholesterol measured at 6 months
11. Ankle Brachial Pressure Index (ABPI) measured at 6 and 12 months and annually thereafter
12. Types of endovascular devices used and/or name of surgery performed (open)
13. Quality-of-life using the EQ-5D-5L measured at 6 and 12 months and annually thereafter
14. Healthcare resource use and costs measured across follow-up assessments over a minimum of 24 months and until the end of the trial

A prospectively planned economic evaluation will be conducted from an NHS and personal social services perspective as per NICE recommendations.

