# STATISTICS AND DATA ANALYSIS

## Sample size calculation

Calculations are based on our published meta-analysis, cohort study across multiple NHS hospitals treating patients with symptomatic PAD and aorto-iliac disease TASC II C and D with endovascular means, and contemporary NHS event rates in our HES analysis specifically for this trial (unpublished data). The perioperative mortality rate (at 30 days) for endovascular treatment is 1% in this unadjusted observational (non-randomised) data and 3% for surgery. Overall, 43% of patients undergoing endovascular treatment for these indications are expected to require re-intervention within 3 years. Based on a 20.63% event rate per year for endovascular treatment regarding amputation and/or death (national HES data), the proportion of patients for this arm free from death and amputation at 3 years is expected to be 50%. Further, based on HES data, the effect of both open surgery and endovascular treatment on the primary outcome is non-linear (more events in the first few months after the intervention), therefore the power calculation is based on an analysis with restricted mean survival time(8). Assuming a 2 year recruitment period and 3 year median follow-up, a sample size of 596 patients (accruing 256 events during follow-up) will provide 90% power (2 sided a=0.05) to detect an absolute risk reduction of 13.3% in terms of event-free survival (death or amputation) at 3 years (50% vs. 63.3% with a hazard ratio of 0.66) between arms (open surgery vs. endovascular treatment). This equates to an increase in restricted mean survival time (for death and/or amputation) of 3 months. Allowing for a conservative 5% loss of follow-up data (based on the completed NIHR HTA BASIL trials and given that the composite comprises of death or major amputation), the final sample size is 628 i.e. 314 participants per trial arm. Patients will be minimised based on age (above 65 years), sex and presence of tissue loss (yes/no) and stratified by site, which are the main factors predicting outcome after treatment for severe symptomatic PAD in multiple studies and similar NIHR HTA trials.

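### Amputation and cardiovascular events are assigned to RMST or Cox with no rule for death, which precludes them and is expected in 30-35% of participants by 3 years

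*Protocol*

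**What the plan says.** Section 11.6 gives the methods for secondary outcomes as "restricted mean survival time or cox proportional hazards regression (as appropriate) for time-to-event outcomes". The qualifier chooses between those two methods and names no third.

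Section 4.2 defines the outcomes concerned. Item 5 is "All lower limb amputations (minor and major i.e. below and above ankle joint) measured in days from randomisation until first event". Item 2 is "Cardiovascular events (myocardial infarction, stroke, admission for heart failure), measured in days from randomisation until first event". Both run "until the end of the trial (minimum 2 years) where no event occurs", and in neither is death part of the event. Section 11.5 adds a further outcome of the same kind: "The individual components of the primary outcome will be reported separately as secondary outcomes".

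The only censoring rule is in section 11.5 and is written for the composite, where death counts as an event: "Participants not experiencing a primary outcome event will have their time to event censored at last follow-up date".

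Death is common in this population. Section 2.2 states: "Three year survival is 70% for open surgery vs. 65% for endovascular treatment (HES data". Section 11.1 gives 30-day mortality of 3% for open surgery and 1% for endovascular treatment. Section 11.6.4, on missing data, does not mention death before an event, and competing risks appear nowhere in the protocol.

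**The concern.** A participant who dies can no longer have an amputation, infarction or stroke. Censoring that participant at death treats the death like a loss to follow-up. The resulting Kaplan-Meier curve, and any RMST taken from it, then describes a hypothetical population in which nobody dies. One minus that curve is not the share of patients who will lose a limb, and it is too high wherever deaths occur.

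The protocol leaves two readings open. Section 4.2, read literally, carries someone who dies without the event forward to the end of the trial as event-free. However, the primary outcome in section 4.1 has the same end-of-trial wording, and section 11.5 turns it into censoring at the last event-free observation. Applied to amputation or cardiovascular events, that convention censors at death. The two readings answer different questions and give different numbers, and both fit the text.

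Sections 2.6 and 14.3 report that death and amputation matter most to patients. The component results will show whether any benefit lies in saved limbs or saved lives, so the limb result should be one that can be read as a risk.

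**Working it through.** **Inputs.** Three-year survival is 65% endovascular and 70% open (section 2.2). Three-year amputation-free survival is "50% vs. 63.3% with a hazard ratio of 0.66) between arms" (section 11.1, endovascular first).

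**The plan's own figures reproduce.** Hazard ratio: ln(0.633)/ln(0.5) = 0.660. Annual endovascular event rate: 1 − 0.5^(1/3) = 20.63%.

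**Assumptions.** Hazards are constant, and mortality is the same before and after amputation. The protocol gives no amputation rate, so the amputation hazard is obtained by subtraction.

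**Hazards per year.**

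| | Endovascular | Open |
|---|---|---|
| Composite, −ln(AFS)/3 | 0.2310 | 0.1524 |
| Death, −ln(survival)/3 | 0.1436 | 0.1189 |
| Amputation, by subtraction | 0.0875 | 0.0335 |

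**Three-year amputation risk.** With a the amputation hazard and d the death hazard:

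- Deaths censored, 1 − exp(−3a): 1 − exp(−0.2624) = 23.1% and 1 − exp(−0.1006) = 9.6%. The difference is 13.5 points.
- Cumulative incidence, a/(a+d) × (1 − exp(−3(a+d))): 0.0875/0.2310 × 0.500 = 18.93% and 0.0335/0.1524 × 0.367 = 8.07%. The difference is 10.9 points before rounding of the arms.

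**Mean time lost to amputation by 3 years (months).**

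- Deaths censored, 12 × [3 − (1 − exp(−3a))/a]: 4.34 vs 1.75, a contrast of 2.6.
- From the cumulative incidence, 12 × a/(a+d) × [3 − (1 − exp(−3(a+d)))/(a+d)]: 3.80 vs 1.56, a contrast of 2.2.

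**Hazard ratio.** The cause-specific ratio is 0.0335/0.0875 = 0.38. The approximate subdistribution ratio at 3 years, ln(1 − 0.081)/ln(1 − 0.189), is 0.40. They barely differ.

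**Sensitivity to the mortality assumption.** If only 50% to 90% of the death hazard acts before amputation (an assumed range), the differences are about 13.6 points with deaths censored against 12.1 to 11.1 points as cumulative incidence.

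**Sensitivity to timing.** Section 11.1 expects more events in the first months. Keep the same 3-year cumulative hazards, but place 50% to 70% of the amputation hazard and 17% to 30% of the death hazard in the first 6 months (assumed). Apply the cumulative-incidence formula in each period, weighting the second by the probability of being alive with the limb at 6 months. The cumulative incidences then range from 19.8% vs 8.4% to 21.1% vs 8.9%, so the difference is 11.4 to 12.3 points against 13.5. The excess is 13.5/12.3 to 13.5/11.4, about 10% to 19%. Under constant hazards it is 13.5/10.85, about 24%.

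**Direction of the distortion** (difference is endovascular minus open, hazards per year):

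| Assumed pattern | Deaths censored | Cumulative incidence |
|---|---|---|
| Amputation 0.06 in both arms, section 2.2 mortality | 0.0 points | −0.5 points |
| Amputation 0.0875 in both arms, whole composite effect on death | 0.0 points | −2.1 points |
| Amputation 0.0875 vs 0.07, death 0.10 vs 0.16 | 4.1 points | 4.9 points |

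In the last row the censored analysis understates the difference.

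**The literal section 4.2 rule.** Simulating the constant hazards above, with the trial ending between 2 and 4.5 years after randomisation and event-free deaths kept at risk until then, gives 18.9% vs 8.1% and a 2.2-month contrast. These are the cumulative-incidence values. Censoring at death gives 23.1% vs 9.6% and 2.6 months.

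No rate is given for cardiovascular events or minor amputations, so those outcomes cannot be quantified.

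**The case against.** The strongest reply is that competing-risk handling of secondary outcomes usually belongs in the analysis plan, which section 11.3 promises, and that section 11.6 never says deaths are censored. Part of this stands: censoring is an inference from section 11.5, not a stated rule. But the protocol does name the methods, and neither RMST nor Cox as named deals with death. Combined with the only censoring convention it provides, the likeliest reading gives the wrong absolute quantity.

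A reader might also infer more than the document supports:

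- *That the between-arm difference is necessarily overstated.* It is under the section 2.2 mortality combined with the design target. Under other mortality patterns the overstatement vanishes or reverses, and early mortality is expected to be higher with open surgery.
- *That the Cox analysis is biased.* Censoring at death gives a valid cause-specific hazard ratio. The error would be to read that ratio as an effect on risk.
- *That section 4.2 commits a second error by crediting people who die with event-free time.* Keeping event-free deaths at risk to the administrative end reproduces the cumulative incidence. Simply ending observation at death and then running RMST would create the problem.

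The magnitude is also fragile. It combines survival that section 2.2 calls unadjusted and observational with a design target for the open arm, and its constant hazards disagree with section 11.1.

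**Conclusion.** The point stands in limited form. The protocol assigns RMST or Cox to outcomes that death precludes, expects 30-35% mortality by 3 years, and has no rule for a death before the event. If deaths are censored, absolute amputation and cardiovascular risks from Kaplan-Meier or RMST are too high in both arms, and the difference between arms is distorted in a direction that cannot be fixed in advance.

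The figures of 13.5 against 10.9 points and 2.6 against 2.2 months illustrate the possible size for amputation. They rest on constant hazards, on mortality unaffected by amputation, and on joining two sources within the protocol. They are not a forecast. The primary composite, all-cause mortality and the sample size are untouched.

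**What to change.** In section 11.6, state that death is a competing event for the amputation component, all lower limb amputations and cardiovascular events. Replace RMST with deaths censored by Aalen-Johansen cumulative incidence for each arm, with the difference in cumulative incidence or in restricted mean time lost and its 95% confidence interval. Label any Cox hazard ratio as cause-specific and show it beside the hazard ratio for death.

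In section 4.2, items 2 and 5, state that a death without the event is recorded as a competing event on the date of death, neither as ordinary censoring nor as further event-free time. Apply the same rule to the amputation component in section 11.5.

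The cost is analysis wording and standard software. Dates of death are already collected for the primary outcome, so no new data are needed.

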### Subgroup analyses

An un-powered exploratory subgroup analyses of the primary outcome will be performed to assess associations between TASC class of aorto-iliac disease, length and location of aortic and iliac occlusions, and types of endovascular treatment (e.g. use of kissing stents aorto-iliac stents, use of covered vs. uncovered stents, and use vs. no use of an aortic stent), based on our published evidence and feedback from NHS survey which strongly supported this exploratory analysis (8, 9).

### Interim analysis and criteria for the premature termination of the trial

There will be no formal interim statistical assessment for early termination of the trial for safety or efficacy. The DMC will monitor accruing trial data for quality and safety concerns and present their recommendations to the TSC. There are no formal stopping rules associated with DMC reporting.

Data collected during the 6 month internal pilot will be presented descriptively in terms of the progression criteria to the oversight committees and funding body and used to assess if it is feasible to continue to recruit to the main study.

### ADVERSE EVENTS REPORTING

Unexpected serious adverse events (SAEs) outside of the list provided in section 9.1, will be reported descriptively in the safety population i.e., participants undergoing trial treatment, presented in groups according to treatment received not as randomised. The number of unexpected serious adverse events and the number of participants experiencing unexpected serious adverse events will be presented categorised by common SAE terms. Unexpected serious adverse events will be presented as line listings and grouped by severity.

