| **Expected SERIOUS Adverse Events** | The following events are considered as expected SAEs. For the purposes of this trial such events do **NOT** require reporting to the EVOCC central team or Sponsor. These events should continue to be recorded in the medical records according to local practice and on the routine follow-up CRFs.   \| Bowel obstruction \| \| --- \| \| Acute kidney injury \| \| Arterial dissection \| \| Arterial pseudoaneurysm formation \| \| Atrial fibrillation (new) \| \| Bowel ischaemia \| \| Chest infection \| \| Diabetes (new diagnosis) \| \| Diabetic foot ulcer (new) \| \| Diabetic ketoacidosis \| \| Endovascular re-intervention (will have to be reported separately using the relevant form) \| \| Failure of endovascular closure device \| \| Fall \| \| Fasciotomy \| \| Haematoma (at site of surgery or percutaneous puncture) \| \| Heart failure (non-fatal) \| \| Hernia \| \| Hypertension (new diagnosis) \| \| Ileus \| \| Intermittent claudication (new diagnosis) \| \| Laparotomy \| \| Lower limb compartment syndrome \| \| Lower limb oedema \| \| Minor amputation (below the ankle joint) \| \| Myocardial infarction (non-fatal) \| \| Need for open surgical access to an artery during the index endovascular procedure \| \| Peripheral embolisation \| \| Peripheral embolisation, not requiring surgery or re-intervention \| \| Prescription of antibiotics for lower limb tissue loss (ulcer/gangrene) \| \| Re-admission to hospital within 30 days of randomisation \| \| Requirement for catheterisation (urinary catheter) \| \| Stent or graft occlusion \| \| Stent or graft thrombosis \| \| Stoma formation \| \| Stroke \| \| Surgical re-intervention (will have to be reported separately using the relevant form) \| \| Transient ischaemic attack \| \| Transient renal replacement therapy \| \| Urinary retention \| \| Urine infection \| \| Use of additional stent or additional endovascular device \| \| Venous thrombosis (deep and/or superficial) \| \| Viral infection \| \| Wound infection \| |

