## Reporting procedures for All serious Adverse Events

### Reporting procedures for Adverse Events

AEs will not be reported as part of this trial. AEs should be recorded in the medical records according to local practice.

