### Reporting Procedures for Serious Adverse Events

Adverse events which meet the serious criteria (SAEs) and which are deemed related to the trial, except those identified as expected within section 9.1, occurring from point of randomisation and until follow-up completion (minimum of two years after trial treatment), must be reported to the Sponsor and the EVOCC trial management team immediately and within 24 hours of becoming aware of the event. The SAE will be reported using the current standard Sponsor SAE reporting form and according to the Sponsor SOP for reporting serious adverse events. For clarity, those listed in the above table as expected SAEs and SAEs that are deemed as **not** related to the trial do not need to be reported, only those events that fall outside of this list should be reported expediently as described. All exempt SAEs should be recorded in the patient medical notes as such.

**Please note:** **No serious adverse reactions (SARs) are anticipated as a unique consequence of participation in the EVOCC trial.**

The following information will be recorded for all SAEs:

- Description of the event
- Date of onset and end date
- Severity
- Assessment of relatedness to trial
- Action taken.

SAEs will be followed until resolution or the event is considered stable.

It will be left to the investigator’s clinical judgment whether or not an SAE is of sufficient severity to require the participant’s removal from the trial. The participant must undergo an end of trial assessment and be given appropriate care under medical supervision until symptoms cease or the condition becomes stable. The severity of events will be assessed on the following scale: 1 = mild, 2 = moderate, 3 = severe. The relationship of SAEs to the trial will be assessed by a medically qualified investigator.

Additional information will be provided if requested to the Sponsor and main Research Ethics Committee (REC). The Principal Investigator or another delegated physician (as agreed by the Sponsor) is responsible for the review and sign off of the SAE and the assessment of causality.

The Sponsor will perform an initial check of the information and ensure that the SAE line listing is reviewed by the Director of Research & Innovation. All SAE information must be recorded on an SAE form and sent to the Sponsor. Additional information received for a case (follow-up or corrections to the original case) needs to be detailed on a new SAE form and sent to the Sponsor.

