Copies of all documentation and correspondence relating to SAEs will be stored in the TMF and ISF.

In addition to the expedited reporting above, the CI shall submit once a year throughout the trial or on request an Annual Report to the Ethics Committee which lists all SAEs that have occurred during the preceding 12 months.

The trends in these events will be independently reviewed in addition to the trial safety monitoring procedures. The decision regarding the frequency of review of individual and cumulative SAEs is to be based on the trial design, risk assessment and advice from the Sponsor / TSC / DMC and will include:

- Clinical review of a line listing of all life threatening or SAEs resulting in death within 1 week of their occurrence
- Clinical review of a line listing of all other SAEs on a monthly basis
- Cumulative review of all safety information by the DMC on an annual basis or more often if required

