## Data Monitoring Committee (DMC)

Independence is a key characteristic of a Data Monitoring Committee where the committee members are completely uninvolved in the running of the trial and thus cannot be unfairly influenced (either directly or indirectly) by individuals or institutions, involved in the trial. The role of the DMC is to monitor outcome data, safety data and other trial data and make recommendations to the TSC on whether there are any ethical or safety reasons why the trial should not continue. The safety, rights and well-being of the trial participants are of paramount importance, in addition to the validity of the trial data. The DMC will also consider data emerging from other related trials, provided by the Sponsor or Funder.

The DMC will consist of an Independent Chair, an Independent Clinician and an Independent Statistician. The DMC will adopt a charter, based on the principle of Damocles, to define its terms of reference and operation. The DMC will meet on annually as specified in the charter or more regularly in response to safety concerns or on recommendations by the committee themselves.

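### The adverse-event tables cover unexpected SAEs only, leaving most listed expected complications with no stated between-arm summary, and the SAE reporting rule cannot supply the required listings of all SAEs

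*Protocol*

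**What the plan says.** **Scope of the tables.** Section 11.6.3 states that "Unexpected serious adverse events (SAEs) outside of the list provided in section 9.1, will be reported descriptively in the safety population". It defines that population as participants who undergo trial treatment and groups them by treatment received, not as randomised. Section 9.2.1 sets non-serious events aside: "AEs will not be reported as part of this trial".

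**Expected SAEs.** Section 9.1 lists events that need not be reported to the central team or the sponsor, but adds: "These events should continue to be recorded in the medical records according to local practice and on the routine follow-up CRFs". Section 9.2.2 says of the same exempt events: "All exempt SAEs should be recorded in the patient medical notes as such". It does not mention the CRF.

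**What sites send in.** Section 9.2.2 limits expedited reporting to SAEs "and which are deemed related to the trial, except those identified as expected within section 9.1", counted from randomisation to the end of follow-up.

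**What oversight must receive.** Section 9.2.2 also requires "Clinical review of a line listing of all life threatening or SAEs resulting in death within 1 week of their occurrence", a monthly listing of all other SAEs, and a yearly report to the ethics committee that lists every SAE of the previous 12 months. Section 10.2 adds: "The role of the DMC is to monitor outcome data, safety data and other trial data".

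**Harms handled as outcomes.** Section 4.2 makes all-cause mortality, a cardiovascular composite, admissions after the index discharge, re-interventions with their nature, and all lower limb amputations secondary outcomes. Section 11.6 analyses secondary outcomes with 95% confidence intervals in the intention-to-treat population.

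**The concern.** The trial compares a more invasive procedure with a less invasive one. The protocol itself says that open surgery carries many perioperative complications (section 1) and that its costs arise partly from early complications (section 2.2). Many such complications are on the expected list. If section 11.6.3 is followed as written, they have no stated between-arm summary unless they also qualify as a secondary outcome.

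The second problem is operational. Section 11.6.2 provides no formal interim analysis and no stopping rules, so the listings in section 9.2.2 are an important input to safety monitoring. They are defined as complete, while the reporting rule that feeds them is selective.

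**Working it through.** The plan gives no figure on this point. The check is therefore a count of the section 9.1 terms against the section 4.2 outcomes, followed by a side-by-side reading of the reporting rules.

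**Step 1: count the terms.** Section 9.1 lists 44 expected SAE terms.

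- *Directly matched to a compared outcome: 7.* Endovascular re-intervention, surgical re-intervention, non-fatal heart failure, minor amputation, non-fatal MI, re-admission, stroke.
- *Possibly caught indirectly: 7.* Acute kidney injury and transient renal replacement (through eGFR); laparotomy, fasciotomy and stoma (as re-interventions); additional stent and open arterial access (through intervention details).
- *The rest.* 44 − 7 = 37 if only direct matches count, and 44 − 7 − 7 = 30 if indirect routes count as well. As shares, 37/44 = 84% and 30/44 = 68%.

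The 30 include bowel ischaemia, bowel obstruction, ileus, chest and wound infection, haematoma, dissection, pseudoaneurysm, embolisation, compartment syndrome, and stent or graft occlusion.

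**Step 2: test the indirect routes.** The admissions outcome starts after the index discharge, so it misses index-stay complications. The first eGFR after baseline is at month 6 (section 4.2 and Table 2), so a perioperative kidney injury that recovers need not show.

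**Step 3: compare what is required with what is supplied.**

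| Output in section 9.2.2 | Scope required | Supplied by the SAE route | Other source |
| --- | --- | --- | --- |
| One-week listing | All fatal or life-threatening SAEs | Related and off-list only | Deaths, from outcome data |
| Monthly listing | All other SAEs | Related and off-list only | Partial, where an event is also an outcome |
| Annual ethics report | All SAEs of the past 12 months | Related and off-list only | As above |

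Deaths are collected at the clinical event reviews in section 8.4.2: discharge, day 30, and months 6, 12, 24, 36, 48 and 54. By the days in Table 2, the gap from month 12 to month 24 is 730 − 365 = 365 days. A site may learn of a death sooner, but nothing in that route delivers it within one week.

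**Step 4: deaths as outcome data.** Section 11.1 gives 30-day mortality of 3% for surgery and 1% for endovascular treatment. With 314 per arm, 314 × 0.03 = 9.4 and 314 × 0.01 = 3.1 deaths. All of these enter the mortality outcome, whether or not they are reported as SAEs.

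**Step 5: fatal cases of listed events.** MI and heart failure are listed as expected only when non-fatal. Stroke and bowel ischaemia carry no such qualifier, so it is unclear whether a fatal case is exempt from reporting.

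**Step 6: population.** SAEs count from randomisation, but the section 11.6.3 table includes only participants who undergo trial treatment. Never-treated participants are left out and crossovers move to the other group. Events before the procedure in people who are later treated stay in.

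**The case against.** The strongest reply is that section 11.6.3 says what will be reported and does not forbid more. A descriptive complications table is commonly left to the SAP, which is not shown, and an as-treated safety population is conventional. The harms that matter most are compared as randomised. Some uncounted terms may also surface elsewhere, such as an occlusion that leads to re-intervention or a late infection recorded as a reason for admission. The 44 terms are also uneven in weight: they include fall, viral infection and new hypertension, and embolisation appears twice.

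Much of this stands. It rules out several stronger readings that a reader might reach:

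- *That the harms separating the arms are never compared.* Death, MI, stroke, heart-failure admission, amputation, re-intervention and later admission are compared by randomised arm.
- *That the listing of deaths cannot be produced, or that the DMC would not see most deaths.* Deaths are endpoint data and outcome data are within the DMC's remit. What is in doubt is the one-week timing.
- *That about 204 deaths would go unlisted.* The sum is 314 × 0.35 + 314 × 0.30 = 204, from the 3-year survival figures in section 2.2. Those are unadjusted observational rates, applied as if all 628 were followed for 3 years, whereas minimum follow-up is 2 years and the median is 3. The protocol also gives no figure for the share of deaths judged unrelated.
- *That events while waiting for treatment are dropped.* This is so only for participants who are never treated, and their deaths remain in the intention-to-treat analysis.
- *That the extra table needs no further data collection.* Section 9.1 supports this, but section 9.2.2 mentions medical notes only, and the CRFs are not shown.

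The reply does not remove the core. Section 11.6.3 states a scope rather than leaving one open, and an SAP cannot repair a reporting rule that sites follow.

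**Conclusion.** The point holds in two limited parts.

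First, as written, roughly 30 to 37 of the 44 expected SAE terms have no stated between-arm summary, and the gap is clearest for complications during the index stay. The range depends on whether indirect routes count. It is a count of terms, not a measure of clinical weight.

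Second, section 9.2.2 conflicts with itself: a rule that sends in only related, off-list SAEs cannot feed listings and a report defined as covering all SAEs. Deaths can be recovered from outcome data, though not reliably within one week. Non-fatal life-threatening SAEs and other SAEs would be incomplete.

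Sections 9.1 and 9.2.2 also differ on whether expected SAEs go on the CRF or only in the medical notes. Neither the primary analysis nor the sample size is affected.

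**What to change.** 1. In section 11.6.3, add a descriptive summary of the CRF-recorded section 9.1 events by randomised arm. It should cover all randomised participants from randomisation, and give numbers of patients and of events, within 30 days of the procedure and overall. Keep the as-treated table of unexpected SAEs as supportive.
2. Reconcile sections 9.1 and 9.2.2 on whether expected SAEs are recorded on the CRF or only in the medical notes, and state whether a fatal case of a listed event is exempt.
3. Reconcile the reporting rule in section 9.2.2 with its own listings. Either feed all deaths by arm from outcome data into the DMC report and the listing, or replace the word *all* with a description of what is actually reported.

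The cost is one extra table and wording changes in three sections, plus confirmation that the CRFs have fields for the listed events. If they do not, step 1 would need added CRF fields.
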